## Abstract

**Introduction:**

Many people with type 1 diabetes struggle to manage their glucose levels and experience stress related to the behavioral demands of the disease. The aim of this study is to investigate whether treatment with a diabetes-educated psychologist can improve glucose levels and decrease diabetes distress.

**Materials and methods:**

Individuals with HbA1c >62 mmol/mol (7.8%) were randomized to either psychological treatment or control group. The study duration for each participant was 52 weeks. Patients who received treatment met with a diabetes-educated psychologist a minimum of seven times. In total 6 outpatient diabetes units and 10 psychologists participated. Cognitive behavioral therapy was primarily the treatment of choice. Both groups met with a diabetes nurse and/or physician at the start of the study and at 3, 6, and 12 months. HbA1c, blood pressure, and weight were measured at scheduled visits. Diabetes distress, quality of life, hypoglycemia confidence, and treatment satisfaction were evaluated using questionnaires. The primary endpoint is the difference in HbA1c from baseline to week 52. Secondary endpoints are changes in diabetes distress and quality of life from baseline to week 52, as well as treatment satisfaction at 52 weeks.

**Discussion:**

This study seeks to improve knowledge about how to support patients who struggle to manage their diabetes. If the results of this study show that psychological treatment has an effect on HbA1c or on diabetes distress, it could indicate that psychologists should become more involved in diabetes care teams. Clinical trial registration: ClinicalTrials.gov ID NCT03753997

## Introduction

1

Type 1 diabetes with suboptimal glucose regulation is connected to a number of serious complications such as cardiovascular disease, retinopathy, neuropathy and nephropathy (1). Research has shown that good glycemic management can significantly decrease risk for complications and mortality (2). There are various strategies to achieve optimal HbA1c, including continuous glucose monitors (CGMs), multiple daily insulin injections (MDI), and insulin pumps. However, many patients still struggle to meet target blood glucose levels.

Recommendations for people with diabetes include adopting a number of self-care behaviors to manage the disease, which many people find challenging (3, 4). This includes frequent monitoring of blood glucose levels as well as following extensive recommendations about diet and exercise (5). Since these behaviors can be demanding and involve many parts of a person’s life, psychosocial and lifestyle factors play an important role in how well people with diabetes manage their disease (5).

Several psychosocial factors have been identified as barriers to good glycemic management, including fear of hypoglycemia, depression, lack of motivation, lack of support, and diabetes burnout (6). The American Diabetes Association reports that 18-45% of people with diabetes experience diabetes distress (5). Diabetes distress refers to the ongoing worries, fears, and challenges of managing a chronic disease, including treatment burden, risk of complications, potential loss of function, and access to care concerns (7). Studies have also shown that depression is 2-3 times more prevalent in people with diabetes compared to the population at large (8). In light of these findings, psychological care has become an important aspect to consider in the overall care for diabetes patients (9). Clinical psychologists in diabetes care teams can contribute by assessing and treating diabetes-related mental health problems, as well as help educate and advise other professions on how to support the psychological wellbeing of patients (9). It is also important for psychologists to be educated on diabetes to be able to understand and treat specific problem areas related to the disease (9).

In recent years, several studies have investigated the effect of different psychological interventions on glycemic management. Results have been mixed, with some studies finding effects on HbA1c and others not. In a recent review (10), no significant effect of psychological interventions was found on HbA1c in both children and adults with type 1 diabetes. Another review published in 2021 examined six randomized controlled trials on adolescents with type 1 diabetes (11). Three studies showed an improvement in glucose levels, while the other three found no significant changes (11). Further, a review from 2018 found psychological interventions that were specifically tailored to people with diabetes (both type 1 and type 2) were effective in improving both HbA1c and diabetes distress (3). A majority of the studies of psychological interventions for adults with type 1 diabetes were given in a group setting and were based on CBT (10). Randomized controlled studies evaluating the effect of individual CBT on HbA1c are however scarce, and the few studies that exist show mixed results. In a large study by Ismail et al. (12) the combination of individual motivational enhancement therapy (MET) and CBT was found to have a positive effect on HbA1c while several studies where CBT was evaluated for comorbid conditions in type 1 diabetes (13–16) found no effect on HbA1c (although on the comorbid condition).

To summarize, the scarcity of randomized controlled trials of the effect on HbA1c of individual CBT delivered by diabetes-educated psychologists suggest a need for more studies, to further increase our understanding of how and when psychological interventions based on CBT can help patients improve glycemic management.

The primary aim of this study is to assess whether treatment by a diabetes-educated psychologist can help patients with high glucose levels improve their HbA1c. A secondary aim is to investigate the effect of psychological treatment on diabetes distress and other psychosocial factors such as quality of life as well as treatment satisfaction. As mentioned above, diabetes distress is a common issue, and many people struggle with finding balance between diabetes and other areas of life. Should the results of this study show an improvement in blood glucose levels and/or psychosocial factors such as diabetes distress, it could be an incentive to start involving psychologists in the treatment of patients with diabetes on a broader scale. The results of this trial may also help guide future research in this area.

## Materials and methods

2

### Study design and locations

2.1

This is a non-blinded, randomized clinical trial with a parallel design. The study was conducted at six diabetes specialty clinics in Stockholm, Gothenburg, Uddevalla, Uppsala, Linköping, and Norrköping. Participants were recruited between January 2019 and December 2023. Results are anticipated to be presented in late 2025 or early 2026. Patients were initially contacted by written correspondence, followed by telephone contact. Patients were randomized 1:1 to either treatment with a diabetes-educated psychologist or conventional care. The study duration for each patient was 52 weeks. Psychological treatment consisted of a minimum of five visits with the psychologist in the first three months and a minimum of two follow-up visits in the following 9 months. A majority of visits were performed face-to-face at the diabetes out-patient clinics. Some visits were performed via video or telephone. A total of 10 diabetes-educated psychologists provided treatment in the study across all six clinics. Both individuals in treatment and control groups visited with a diabetes nurse at randomization, 3 months, 6 months, and 1 year. Extra visits with a diabetes nurse could be scheduled, if necessary, in the event of very high HbA1c. Both groups also met with a physician at the screening visit and at 1-year follow-up.

### Eligibility criteria

2.2

All participants gave verbal and written informed consent before participating. The study was approved by the Swedish Ethical Review Authority.

The study included adults with type 1 diabetes and HbA1c >62 mmol/mol (7.8%). All inclusion and exclusion criteria are listed in **Table 1**.

**Table 1 T1:** Inclusion/exclusion criteria.

Inclusion criteria
Informed consent obtained before trial-related activities Type 1 diabetes Age >18 years HbA1c >62 mmol/mol (7.8%)

Exclusion criteria
Type 2 diabetes Diabetes duration <1 year Long-term systemic glucocorticoid treatment during the last 3 months Treatment changes in the last 3 months (e.g., MDI vs insulin pump, started or stopped CGM or FGM therapy) Planned move or travel in the next 12 months that would interfere with study participation Current or planned pregnancy or breastfeeding during the next 12 months Other reasons determined by investigator (e.g., severe psychiatric conditions, alcohol/substance misuse etc.)

### Randomization

2.3

Participants were randomized using a centralized web system that was handled by Statistiska Konsultgruppen Sweden. Every patient was assigned a unique and anonymous subject ID. The system was balanced for age, sex, and HbA1c.

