#### Primary efficacy analysis

2.6.2

The primary efficacy analysis is the change in HbA1c from baseline to 52 weeks follow-up between the two groups using analysis of covariance (ANCOVA) with HbA1c at baseline as covariate in the ITT population, two-sided test of significance level 0.05.

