#### Secondary efficacy analysis

2.6.3

The secondary efficacy analysis is the change in diabetes distress scale (DDS) score from baseline to week 52 in the two treatment groups using ANCOVA with DDS score at baseline as the covariate. In case the assumption of normal distribution is not met, an effort to transform data to normal distribution will be made. If the assumption of normal distribution is still not met after transformation of data, logistic regression will be used with grouping variable as the dependent variable, change in DDS as main effect variable, and DDS score at baseline as the covariate.

Change in the quality-of-life score from baseline to week 52 between the two treatment groups will be analyzed using the same methodology as for the DDS score.

DTSQc score at week 52 between the two treatment groups will be analyzed using ANCOVA in case the assumption of normal distribution is met, or otherwise by using the Mann-Whitney U-test.

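### Age and sex balance the allocation but enter no stated model, and HbA1c is also missing from the DDS and ADDQoL models; if these factors are prognostic, the tests are mildly conservative and some precision is lost

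*Protocol article*

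**What the plan says.** Section 2.1 of the protocol article states 1:1 allocation: "Patients were randomized 1:1 to either treatment with a diabetes-educated psychologist or conventional care". Section 2.3 (Randomization) adds "The system was balanced for age, sex, and HbA1c". It does not give the method, any categories for age or HbA1c, or the size of any random element.

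The stated models are:

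- **Primary (section 2.6.2):** change in HbA1c at week 52, "using analysis of covariance (ANCOVA) with HbA1c at baseline as covariate in the ITT population", with a "two-sided test of significance level 0.05".
- **DDS (section 2.6.3):** "using ANCOVA with DDS score at baseline as the covariate".
- **ADDQoL (section 2.6.3):** "will be analyzed using the same methodology as for the DDS score".
- **DTSQc (section 2.6.3):** "DTSQc score at week 52 between the two treatment groups will be analyzed using ANCOVA in case the assumption of normal distribution is met", and otherwise a Mann-Whitney test. No covariate is named, and Table 3 lists DTSQc only as a week-52 score.
- **Exploratory endpoints (section 2.6.4):** adjustment for baseline values.

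Age and sex appear in none of these models. Baseline HbA1c appears in the primary model but not in the DDS or ADDQoL model.

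**The concern.** Balancing an allocation on a factor removes most of that factor's contribution to the chance difference between arms. If the factor is then left out of the analysis, its variance stays in the residual. The model-based standard error therefore describes a trial with more chance imbalance than this one can have. Confidence intervals come out too wide, the true type I error falls below 5%, and precision that the design has secured is not used.

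What is at stake is efficiency and correctly calibrated intervals. The effect exists only if the omitted factors predict the outcome once the model's own covariate is accounted for.

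**Working it through.** **1. The plan's own sample size.** Inputs from section 2.6.1: difference 4.4 mmol/mol (0.4 percentage units), SD of change 8.7 mmol/mol (0.8%), power 80%, alpha 0.05 two-sided.

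- Normal approximation: n per arm = 2 × (1.960 + 0.842)² × (SD/difference)². This gives 61.4, so 62, in mmol/mol, and 62.8, so 63, in percentage units.
- Two-sample t-test: 62.3 and 63.8, so 63 and 64.
- Drop-out: 128 / 0.9 = 142.2.

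The stated 64 per group and 142 in total are reproduced. The calculation uses the unadjusted SD of change and takes no credit for any covariate.

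**2. Effect of omitting balanced factors.** Let R² be the share of residual variance, given the covariate already in the model, that the omitted factors explain. The article gives no value, so R² is assumed over a range. With near-perfect balance:

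- model SE / true SE = 1/√(1 − R²)
- actual type I error = 2 × [1 − Φ(1.960/√(1 − R²))]
- power, factors omitted = Φ((δ − 1.960)/√(1 − R²))
- power, factors included = Φ(δ/√(1 − R²) − 1.960)

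Here δ = 4.4 / (8.7 × √(2/64)) = 2.861. The planning SD of 8.7 is taken as the residual SD before age and sex are added. Both power columns use the normal approximation.

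| Assumed R² | SE too large by | Type I error, omitted | Power, omitted | Power, included |
|---|---|---|---|---|
| 0 | 0% | 5.0% | 0.816 | 0.816 |
| 2% | 1.0% | 4.8% | 0.819 | 0.824 |
| 5% | 2.6% | 4.4% | 0.822 | 0.835 |
| 10% | 5.4% | 3.9% | 0.829 | 0.854 |

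The power forgone is about 0, 0.5, 1.3 and 2.6 percentage points.

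**3. Simulation check.** The set-up was minimisation with probability 0.8 on two-level age, sex and HbA1c, 128 participants, and ANCOVA with and without age and sex. There were 4,000 runs under the null and 2,000 under the alternative.

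- At R² = 10%, type I error was 0.041 with the factors omitted and 0.050 with them included. Power was 0.816 and 0.845. The mean model SE without the factors was 0.1769 against an empirical SD of 0.1697, a ratio of 1.042. This is below the 1.054 for perfect balance, so the table's SE figures are upper limits.
- At R² = 2% and 5%, type I error with the factors omitted was 0.052 and 0.051. The Monte Carlo standard error is about √(0.05 × 0.95/4000) = 0.003, so the simulation cannot separate effects this small from none.

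**4. Secondary endpoints.** The SE and type I columns apply to any linear model for the R² that holds there. The power columns do not, because the article gives no planning figures for DDS, ADDQoL or DTSQc.

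**The case against.** The strongest objection is that the loss may be negligible. The primary model already contains baseline HbA1c, one of the three balancing factors. Nothing in the article shows that age and sex predict week-52 HbA1c beyond it. At R² = 0 nothing is lost, and at 2% the standard error is only 1% too large. This stands, and it makes the point conditional and modest.

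A second objection is that the article condenses a fuller protocol, and a statistical analysis plan that is not shown may name more covariates. That carries less weight, because sections 2.6.2 and 2.6.3 name the covariates for the primary, DDS and ADDQoL models. A plan that added more would depart from the published models.

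Third, the trial is non-blinded and recruitment ended in December 2023, so a late change of model could look data-driven. This stands and governs how the fix is made.

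A reader might infer three stronger things that the documents do not support:

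- **That the result is biased or the false-positive rate inflated.** In a linear model with randomized allocation, omitting balanced factors biases nothing, and the error goes in the conservative direction.
- **That the trial is underpowered.** The sample size does not rely on adjustment, and calculated power at 64 per arm stays above 0.80 in every row of the table.
- **That clinic must be added for the same reason.** Clinic is not named as a balancing factor, so this mechanism does not apply to it. Nor does clinic identify the psychologist, since ten psychologists worked across six clinics.

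**Conclusion.** The mismatch is in the text: age and sex restrict the allocation but appear in no stated model, and HbA1c is also absent from the DDS and ADDQoL models. The consequence is mildly conservative inference and some lost precision, to the extent that the omitted factors are prognostic.

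For an assumed R² of 0 to 10%, the standard error is at most 0 to 5.4% too large, type I error is 5.0 to 3.9%, and up to 2.6 points of power are forgone in the primary analysis. These figures assume near-perfect balance, a linear model and 64 per arm with SD 8.7 mmol/mol. They do not carry over directly to the logistic-regression or Mann-Whitney fallbacks in section 2.6.3. The change is worth making because it is cheap, not because the primary conclusion is at risk.

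**What to change.** - **Primary ANCOVA:** add age and sex to baseline HbA1c.
- **DDS and ADDQoL ANCOVAs:** add age, sex and baseline HbA1c to the endpoint's own baseline.
- **DTSQc ANCOVA:** name age, sex and baseline HbA1c as the covariates, since no baseline DTSQc score is listed to adjust for.

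State the form in which age enters. Record the change and its reason in a documented amendment, dated relative to data access and made before the outcome data are analysed. If that moment has passed, keep the published models and report the fuller ones as labelled sensitivity analyses.

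The cost is two degrees of freedom in the primary model and three in each of the others, plus the amendment. With 128 completers, residual degrees of freedom in the primary model fall from 128 − 3 = 125 to 128 − 5 = 123. No new data are needed, because the three factors were used for the allocation.

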### Treatment

2.4

#### Clinical visits

2.4.1

After inclusion and randomization, individuals in both treatment and control groups met with a diabetes nurse at 13, 26, and 52 weeks. A physician was also present for the inclusion visit and the 52-week follow-up where physical examinations were performed. At each follow-up visit HbA1c, blood pressure, and weight were measured. Insulin type and doses, type of glucose monitoring, and insulin delivery method were also checked, as well as the occurrence of adverse events. At randomization and at 26 and 52 weeks, diabetes distress was measured using the Diabetes Distress Scale (DDS) (17), which summarizes overall level of diabetes distress, as well as the level in specific areas. Quality of life was measured using the Audit of Diabetes Dependent Quality of Life (ADDQoL) (18), which measures present quality of life, the impact of diabetes on quality of life, and the average weighted impact of 19 different areas in life and how they are affected by diabetes. Hypoglycemia confidence was measured using the Hypoglycemia Confidence Scale (HCS) (19) which is a 9-item self-report scale which evaluates confidence in preventing and addressing hypoglycemic events, and treatment satisfaction was measured using the Diabetes Treatment Satisfaction Questionnaire status and change version (DTSQs and DTSQc) (20, 21), containing eight items scored on 7-point scales that are summed to a total treatment satisfaction score.

#### Diabetes education for psychologists

2.4.2

All psychologists participating in the study were educated in cognitive behavioral therapy (CBT), which was the treatment of choice. Psychologists were also educated about type 1 diabetes before they could start treating patients within the study. The goal of the education was for the psychologists to have an overall understanding of the medical treatment of type 1 diabetes, as well as common psychosocial difficulties connected to the disease.

Education included seminars and self-studies about central aspects of diabetes care such as basic glucose physiology, hypoglycemia, insulin treatment (with injections or insulin pumps), risk factors, complications, glucose-monitoring and self-care recommendations. A psychologist with experience in treating patients with diabetes provided education on psychological aspects of diabetes treatment and common psychosocial barriers to glycemic management. All psychologists also participated in 20-25 clinical visits with a diabetes nurse or doctor. In addition, psychologists wore CGMs and insulin pumps (without insulin) themselves for 2-3 days in order to gain personal experience with some of the day-to-day tasks of living with diabetes, such as monitoring glucose levels and managing necessary medical equipment.

#### Intervention by psychologist

2.4.3

Psychological treatment consisted of a minimum of five visits within the first three months and a minimum of two follow-up visits within nine months. However, more visits could be added if the psychologist and patient agreed on the need for more.

Psychologists were advised to start treatment with a clinical interview to gain understanding of participants’ individual circumstances and problem areas. A number of common psychosocial barriers to glycemic management were reviewed in the interview, see **Table 2**.

**Table 2 T2:** Problem areas.

Problem area	Explanation
Depression	Current or previous depressive episodes
“No big deal”	Feeling that diabetes complications are not that serious
Inevitability	Feelings of hopelessness or that complications are inevitable regardless of one’s actions
Treatment skepticism	Dissatisfaction with, or lack of confidence in, one’s treatment plan
Poor social support	Lack of personal network to provide practical and emotional support
Unrealistic plans for action	Setting unrealistic expectations for oneself, e.g., always having perfect blood sugar levels, never eating anything unhealthy etc.
Environmental problems	Things in the home or work environment that make it difficult to take care of one’s diabetes
Denial of disease situation	Denial of the seriousness of the disease. Avoiding diabetes-related things or tasks, i.e., not looking at blood sugar levels, not attending hospital visits etc.
Lack of motivation	Struggling with motivating oneself to adopt necessary self-care behaviors
Problems regarding eating behaviors	E.g., eating large meals, eating even when one is not hungry etc.
Interpersonal or relational problems	Difficulties setting boundaries with others, or asking others for help when needed
Unrealistic fear of hypoglycemia	Avoiding low blood sugars, i.e., by not taking enough insulin. The fear is sometimes rooted in previous experiences.
Psychiatric conditions	Specific psychiatric conditions such as autism, ADHD, eating disorders, or personality disorders that may impact the ability to manage one’s diabetes

The interview also included screening questions for history of psychiatric problems. All participants completed the Patient Depression Questionnaire (PHQ-9) during the first visit with the psychologist (22), which is a tool for screening of depression. In the case of severe depression, the treating physician was consulted to determine where the patient should receive treatment.

The psychologist and participant formulated a treatment plan together, based on the problem areas identified in the interview, and reviewed during the course of treatment if necessary. CBT was the first choice of treatment, but other psychological treatment methods could be used if deemed appropriate by the psychologist. At specific diabetes-related questions the psychologist had the possibility to communicate with the diabetes nurse treating the patient. Visits were primarily performed as physical visits but could be performed digitally when needed.

